### User satisfaction questionnaire

A self-designed questionnaire was developed to assess the user satisfaction of Featback, such as the perceived quality of the support, whether Featback helped them to deal more effectively with their eating problems, and how satisfied they are with Featback in general. Participants are also asked to rate the individual components of Featback and to provide negative and positive comments about Featback.

### Compliance

Two measures of compliance will be extracted from the database. The first measure of compliance will be the number of times a participant has completed the weekly monitoring assessment. The second measure of compliance will be the number of times a participant has completed a monitoring assessment after a completed assessment in the previous week. This second measure of compliance is important because Featback is only programmed to compare obtained results with those of the previous week, not with those completed at earlier points in time. Thus, in case one has missed a monitoring assessment, but completes the next monitoring assessment a week later, results of the completed assessment cannot be compared to the previous results (e.g., results of the previous week are missing). Subsequently, progress or deterioration cannot be accurately monitored, which in turn can produce more general and less individually tailored feedback. To be able to further investigate dose–response relationships, the number of support sessions a participant has received will be recorded as well.

### Attrition follow-up questions

According to Eysenbach [43], there are two different processes of attrition; “dropout attrition” refers to participants being lost to follow‒up, thus not returning follow‒up questionnaires and “non-usage attrition” refers to participants who stop using the intervention. To be able to investigate the reasons for both dropout and non-usage attrition, two attrition follow-up questions are designed: one in case participants fail to complete monitoring assessments and another one in case participants fail to complete the T1, T2, or T3 assessment.

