#### Assessments

All assessments are self-reported and will be conducted online. Table 1 depicts an overview of the assessment instruments that will be used throughout each stage of the study. Primary outcome measures are disordered eating behaviors and attitudes (SEED, EDE-Q) [23,27]. Secondary outcome measures contain ED-related quality of life (ED-QOL) [28], self-stigma of seeking help [29], self-esteem, mastery and support [30], symptoms of depression and anxiety (PHQ-4) [31], repetitive negative thinking (PTQ) [32], motivation to change [33,34], and user satisfaction, as well as compliance and help-seeking attitudes and behaviors. Cost-effectiveness will be evaluated by means of the reported quality of life (EQ-5D) [35] and medical and societal costs (Trimbos/iMTA Questionnaire for Costs Associated with Psychiatric Illness: TiC-P) [36].

**Table 1 T1:** Overview of the assessment instruments used throughout each stage of the study

**Assessment**	**Screening**	**T0: Baseline**	**Weekly monitoring: even weeks**	**Weekly monitoring: uneven weeks**	**T1: Post-intervention**	**T2: 3-month follow-up**	**T3: 6-month follow-up**^2^
Weight Concern Scale (WCS)	X	-	-	-	-	-	-
Short Evaluation of Eating Disorders (SEED)	X	X	-	-	X	X	X
Short Evaluation of Eating Disorders II (SEED-II)	-	-	X	X	-	-	-
Demographics and other information	-	X	-	-	-	-	-
Monitoring questionnaire	-	-	X	X	-	-	-
Patient Health Questionnaire 4 (PHQ-4)	-	X	-	X	X	X	X
Perseverative Thinking Questionnaire (PTQ)	-	X	-	X	X	X	X
Eating Disorder Examination Questionnaire (EDE-Q)	-	X	-	-	X	X	X
Self-stigma of seeking help	-	X	-	-	X	X	X
Self-esteem, mastery and support	-	X	-	-	X	X	X
Eating Disorder-related Quality of Life (ED-QOL)		X	-	-	X	X	X
Motivation to change	-	X	-	-	X	X	X
Session Rating Scale (SRS)	-	-	X^1^	-	-	-	-
User satisfaction questionnaire	-	-	-	-	X^2^	-	-
Attrition follow-up question	-	-	X^3^	X^3^	X^3^	X^3^	X^3^
Help-seeking attitudes and behavior questionnaire	-	-	-	-	X	X	X
Quality of life (EuroQol: EQ-5D)	-	X	-	-	X	X	X
Trimbos/iMTA questionnaire for costs associated with psychiatric illness	-	X	-	-	X	X	X

^1^Only asked after participants’ first week of participation.

^2^Not sent to participants who are randomized to the waiting list control condition.

^3^Sent to participants who fail to complete the monitoring assessment, or the T1, T2 or T3 assessment, respectively.

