### Short Evaluation of Eating Disorders (SEED)

The SEED [23] is a brief self-report measure for the assessment of key ED symptoms. It assesses the three main symptoms of anorexia nervosa (degree of underweight, fear of weight gain, and distortion of body perception) and bulimia nervosa (amount of binge eating, amount of compensatory behavior, and over concern with body shape and weight). Total severity indexes can be calculated for each of the two diagnoses (range 0–3), with higher scores reflecting higher severity indexes. The behavioral measures (bingeing, excessive exercising, and compensatory behaviors) are assessed over the previous four weeks. The SEED has demonstrated construct validity and criterion-related validity, and was furthermore shown to be sensitive to symptom change [23].

Given that the SEED will be administered every week during the intervention period as well, the four-week timeframe for the behavioral measures is adapted to a timeframe of one week. This adapted questionnaire will be referred to as SEED-II.

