### Sample size

The sample size calculation is based on an expected small between-group effect size (Cohen’s *d* = 0.32) [45]. The calculation is conducted by the software program Power Analysis and Sample Size (PASS, 2008). The primary analysis will concern the hypothesis that the average post-intervention level of eating pathology in the waiting list control condition is higher than the average level of eating pathology in the three active intervention conditions. Assuming an alpha of 0.05 and a power of 0.80 (β-1) in a one-way ANOVA study, we need sample sizes of 79 participants in each of the four groups whose means are to be compared using a planned comparison. Taking into account a baseline variable (e.g., T0 assessment) for which we assume a Pearson correlation of 0.5 with the outcome variable, and thus explaining 25% of the variance of the outcome variable, the sample size per group can be reduced by 25% and is thus calculated as 0.75 × 79 = 60 per group. In order to account for dropout, recently reviewed to be approximately 30% for Internet-based interventions [46], the definitive number of participants we will need to recruit is 10/7 × 60 = 86 participants per group, resulting in 344 in total.

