## Discussion

One of the strengths of this study is the evaluation of the (cost-) effectiveness of the intervention, as well as the evaluation of the (cost-) effectiveness of the different levels of support. To our knowledge, this has not yet been investigated in the field of ED.

Both a strength and a limitation of this study is that participants only have to meet three eligibility criteria (16 years of age or older, mild ED symptoms or at risk for the development of an ED, and internet access). A possible limitation could be the influence of comorbid disorders or the use of co-interventions or medication on study outcome measures; a possible strength is that many individuals who suffer from an ED have comorbid mental health problems such as depression, anxiety, substance dependence, and personality disorders [51,52]. Therefore, the broad inclusion criteria may well bear a close resemblance to reality, enhancing the external validity of the results, as well as being consistent with the aim of an applicable and easily accessible intervention for a broad population of individuals with symptoms of ED.

Another characteristic of this study that is both a strength and a limitation, is that measurements are conducted solely online. The advantages that come with online assessments are a reduction in research costs, maximization of the accessibility of participation, and participant anonymity. However, the lack of face-to-face assessment(s) also means a lack of a diagnostic interview, and may furthermore reduce the commitment to the study and the intervention. In order to maximize compliance, motivational reminders will be sent repeatedly, and individuals who complete all study assessments will take part in a lottery including gift vouchers and an iPod.

One of the limitations of this study concerns the lack of a 6-month follow-up for participants in the WLC, given that they will receive Featback with infrequent support from a coach after T2. This means that the relative long-term effectiveness of Featback, as compared to a WLC condition, cannot be examined. Fortunately, the longer-term follow-up data of the different forms of feedback (without support, with infrequent support, and with frequent support) will be available and examined.

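### The contact after a missed T1, T2 or T3 is described as asking for reasons only; offering the brief SEED with it would be a cheap way to recover some primary outcome data

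*Protocol article*

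**What the plan says.** - **Purpose of the contact** (Attrition follow-up questions): "To be able to investigate the reasons for both dropout and non-usage attrition, two attrition follow-up questions are designed". One covers missed monitoring, and there is "another one in case participants fail to complete the T1, T2, or T3 assessment".
- **Recipients** (Assessments, Table 1, footnote 3): "Sent to participants who fail to complete the monitoring assessment, or the T1, T2 or T3 assessment, respectively". The table attaches no outcome instrument to that contact.
- **Primary outcome** (Assessments): "Primary outcome measures are disordered eating behaviors and attitudes (SEED, EDE-Q"), both self-reported online. The SEED section adds: "The SEED [23] is a brief self-report measure for the assessment of key ED symptoms".
- **Primary hypothesis** (Sample size): that "the average post-intervention level of eating pathology in the waiting list control condition is higher than the average level" in the three active conditions. The time point is therefore T1.
- **Planned loss** (Sample size): "In order to account for dropout, recently reviewed to be approximately 30% for Internet-based interventions [46"], the number per group is raised from 60 to 86.
- **Other retention measures** (Discussion): "motivational reminders will be sent repeatedly, and individuals who complete all study assessments will take part in a lottery".
- **Analysis** (Statistical analyses): intent-to-treat and completers analyses, with linear mixed models for effectiveness.

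**The concern.** The trial already sends a message to the people it expects to lose. As described, that message asks why they stopped but not how they are. Reasons for dropout help to interpret attrition, but they cannot take the place of a missing score.

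A larger sample restores the number of analysed participants. It does not remove bias if the chance of missing T1 depends on the outcome or on the arm. The mixed model then has to represent the missing T1 values from what was observed, under a missing-at-random assumption. What was observed probably differs by arm. The active arms are sent the weekly SEED-II, whereas no weekly monitoring is described for the waiting list, and the crisis management section refers to screening data only for that arm. The waiting list is one side of the primary comparison, so outcome data from its initial non-responders would be especially useful.

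The full assessment is not short, so a brief alternative could plausibly draw some replies that the full one does not.

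**Working it through.** **1. The plan's own sample size.** Inputs from the Sample size section: d = 0.32, alpha 0.05, power 0.80, four equal groups, waiting list against the three active groups pooled. With n per group the variance of the contrast is σ²(1/n + 1/(3n)) = 4σ²/(3n), so n = (4/3)(z_alpha + z_power)²/d².

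- One-sided 0.05: (4/3)(1.645 + 0.842)²/0.1024 = 80.5, so 81. This is within two of the stated 79.
- Two-sided 0.05: (4/3)(1.960 + 0.842)²/0.1024 = 102.2, so 103. This does not match 79, although the Statistical analyses section sets a two-tailed level. That is a separate matter; here it only means that power is shown both ways below.
- Baseline covariate: 0.75 × 79 = 59.25, taken as 60.
- Dropout: 60 × 10/7 = 85.7, so 86; 4 × 86 = 344. The inflation is correct.

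**2. Expected T1 loss.** 86 − 60 = 26 per group.

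**3. What a short form might recover.** The document gives no recovery rate, so one fifth to one half is an assumption.

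- One fifth: 26/5 ≈ 5, so 65 per group. Variance ratio 60/65 = 0.92, a fall of about 8%.
- One half: 26/2 = 13, so 73 per group. Variance ratio 60/73 = 0.82, a fall of about 18%.

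**4. The same in power.** This uses d = 0.32, residual SD √0.75, and 86 × (1 − 0.30 × (1 − r)) analysed per group for recovery r.

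| Recovery r | Analysed per group | Power, one-sided | Power, two-sided |
|---|---|---|---|
| 0% | 60 | 0.80 | 0.70 |
| 10% | 63 | 0.81 | 0.72 |
| 25% | 67 | 0.83 | 0.74 |
| 50% | 73 | 0.86 | 0.78 |

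**5. Why these gains are upper bounds.** Steps 3 and 4 count only participants with a T1 value. A mixed model also takes some information from a T1 non-responder's other waves: the baseline SEED, which everyone has because randomisation follows the baseline questionnaire, and the T2 SEED where it is given. The true gain in precision is therefore smaller.

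**6. Burden of the full assessment.** Item counts that the article states: PHQ-4 4, PTQ 15, self-stigma 10, self-esteem, mastery and support 4 + 4 + 2 + 4 = 14, ED-QOL 25, motivation 3, EQ-5D 5. The sum is 76. The EDE-Q, the SEED, the cost questionnaire and the help-seeking questions come on top, as does user satisfaction at T1 in the active arms.

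**The case against.** The strongest reply is that nothing in the plan is wrong here, and much of that reply stands.

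- **A reader might infer that non-responders are contacted only to be asked why.** The article does not support this. It provides repeated reminders and a prize draw, and does not say whether the reminders continue after a missed assessment or whether the attrition message also re-offers the questionnaire. However, a reminder asks for the same full assessment, and the draw is for those who complete everything. Neither is a shorter route to the SEED.
- **A reader might infer that a participant must finish the whole battery or contribute nothing.** The article gives neither the order of the questionnaires nor whether partial answers are saved. The 76 items show burden, not all-or-nothing capture.
- **A reader might infer that dropouts have no outcome data.** They have a baseline SEED, may return at T2, and in the active arms may have SEED-II scores up to week 8. SEED-II uses a one-week frame, so it is not a full substitute.
- **The recovery rate has no source.** It would apply to people who had already let reminders pass. At 10% recovery the gain is only one to two points of power.
- **Late responders are not the same as those who never reply.** Comparing them with full completers informs the missing-at-random assumption but cannot test it.

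It could also be said that a journal article leaves such details to the full protocol. That holds for the handling of reminders and partial forms. It does not dispose of the point, because the article itself states the contact, its recipients and its purpose.

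**Conclusion.** The point holds as a low-cost improvement. The attrition contact at T1 to T3 is described as collecting reasons, no short route to the primary outcome is described, and a brief primary outcome instrument is at hand. It is not an error or a contradiction, and no stated figure is wrong because of it.

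The size is modest and conditional. If one fifth to one half of the 26 expected non-responders per group replied, 5 to 13 more would have a T1 SEED, and the variance of that contrast would fall by at most about 8% to 18%. This rests on the plan's 30% dropout, on the assumed reply rate, and on counting T1 values alone. The further benefit is some outcome information from initial non-responders, collected in the same way in every arm. That benefit cannot be put into a number from the document.

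**What to change.** 1. After the normal reminders have run out, offer the SEED together with the attrition question, in all arms at T1 and T2 and in the three active arms at T3 (the waiting list has no T3). State how this message relates to the reminders.
2. Record the completion date and flag these answers as late short-form responses.
3. Include them in the intent-to-treat mixed model for the SEED, with a sensitivity analysis that excludes them.
4. Compare their scores with those of full completers, by arm, and report this as supportive, not conclusive, evidence on missing at random.

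The cost is one existing brief questionnaire added to an existing online message. There are four downsides:

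- Late answers shift the four-week window of the SEED behaviour items, which is why the date and the sensitivity analysis are needed.
- A few participants may choose the short form over the full assessment, at the expense of the EDE-Q and the cost-utility data. Offering it only after the reminders limits this.
- The EDE-Q, the other primary measure, is not recovered.
- The Trial status section reports enrolment as complete, so the change can apply only to assessments still outstanding. Earlier and later participants would then differ in how the SEED was collected.

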### Help-seeking attitudes and behavior questionnaire

Several questions will be used to assess participants’ help-seeking attitudes and behavior, for example, whether participants generally believe that professional help is beneficial and whether they believe that they need to seek professional help themselves. Furthermore, the questionnaire investigates whether participants intended to seek professional help and whether they actually sought professional help. Regarding the latter, the participants are also asked whether Featback has contributed to the decision to seek help.

### Quality of life

The EuroQol (EQ-5D) [35] generic health index is a standardized, patient-completed instrument which consists of five dimensions: mobility, self-care, usual activities, pain/discomfort, and anxiety/depression. Each dimension can be rated on three levels (no problems, some problems, and extreme problems). Thus, 243 distinct health states are defined, each with a unique utility score, ranging from 1 (‘perfect health’) to 0 (‘death’).

### Sample size

The sample size calculation is based on an expected small between-group effect size (Cohen’s *d* = 0.32) [45]. The calculation is conducted by the software program Power Analysis and Sample Size (PASS, 2008). The primary analysis will concern the hypothesis that the average post-intervention level of eating pathology in the waiting list control condition is higher than the average level of eating pathology in the three active intervention conditions. Assuming an alpha of 0.05 and a power of 0.80 (β-1) in a one-way ANOVA study, we need sample sizes of 79 participants in each of the four groups whose means are to be compared using a planned comparison. Taking into account a baseline variable (e.g., T0 assessment) for which we assume a Pearson correlation of 0.5 with the outcome variable, and thus explaining 25% of the variance of the outcome variable, the sample size per group can be reduced by 25% and is thus calculated as 0.75 × 79 = 60 per group. In order to account for dropout, recently reviewed to be approximately 30% for Internet-based interventions [46], the definitive number of participants we will need to recruit is 10/7 × 60 = 86 participants per group, resulting in 344 in total.

### Statistical analyses

All statistical analyses will be performed in SPSS version 19. A two-tailed significance level of *α* = 0.05 will be used throughout the analyses. Both intent-to-treat and completers analyses will be conducted. Intent-to-treat analyses will include every participant who is randomly allocated to the intervention, regardless of withdrawal or deviation from the protocol [47]. Someone will be considered a completer in case he/she has completed both T0 and T1 assessments, and at least five monitoring assessments.

Pre-treatment differences between the conditions will be investigated using *χ*^*2*^ tests for categorical variables and ANOVAs for continuous variables. Linear mixed model analyses will be used to investigate the effectiveness and maintenance effects of Featback. Time contrasts will be created by means of dummy-coding. Within- and between-group effect sizes (Cohen’s *d*) [48] will be calculated based on the pooled standard deviation. As recommended by Frazier, Tix and Barron [49], potential categorical predictor or moderator variables will be dummy coded, and potential continuous predictor or moderator variables will be standardized. A significant two-way interaction between predictor and time indicates a predictor effect. A significant three-way interaction between time, condition and moderator, indicates a moderator effect. Significant moderator effects of continuous variables will be interpreted by dichotomizing the moderator variable into subgroups of participants who score either low or high (e.g., below or above the sample mean) on the moderator variable. Separate mixed model analyses will then be repeated to examine interactions between condition and time within the low and high subgroups.

A cross-lagged panel design will be used to determine whether changes in mediator variables predict changes in ED symptoms, and not vice versa, as described by Burns et al. [50]. For all outcome and mediator variables, residualized change scores will be calculated for baseline (T0) to mid-intervention (week 4), as well as for mid- (week 4) to post-intervention (T1: week 8). Hereafter, hierarchical regressions will be performed, with mid- to post-intervention standardized change of the primary outcome measure as dependent variable, pre- to mid-intervention standardized change of the primary outcome measure, and mid- to post-intervention standardized change of the mediator variable as independent variables in the first step. In the second step, pre- to mid-intervention standardized change of the mediator variable will be entered into the regression equation. In addition, the inverse association (whether changes in the primary outcome variable predict changes in the mediator variable) will be tested and should not be significant.

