### Support from a coach

Participants will be able to schedule support sessions through different mediums: e-mail, chat or Skype. Coaches will be instructed to e-mail participants in case participants do not schedule any appointments or in case participants do not show up at scheduled support sessions, and to repeat this process twice per non-response. Chat and Skype sessions will imply 20 minutes with a coach. An e-mail session will contain one reply by e-mail from the coach to the participant (who will be instructed to e-mail his/her coach beforehand). The methodology of chat sessions is based on a 5-phase model, containing i) a warm welcome, ii) clarifying of the question, iii) determining the goal of the conversation, iv) concrete elaboration of the goal of the conversation, and v) closing the circle. More detailed information on this model can be found in the handbook written by Schalken et al. [26]. E-mail support is based on the following phases: i) extracting the question, ii) formulating an answer, and iii) checking/re-reading the message and sending it. All coaches will follow an intervention protocol that includes all guidelines for the provision of support.

Support will be provided by master level students in clinical psychology or individuals with a degree in the field of psychology. All coaches will undergo an intensive two-day training from an external company (‘Stichting E-hulp’), specifically focused on the delivery and methodology of online support. Coaches will be taught the basic principles for delivering online support and they will practice with case materials throughout the training. Monthly face-to-face supervision sessions will be organized by the main researcher, a psychologist and an experienced psychotherapist as a matter of routine professional and ethical care, as well as to reinforce adherence to the protocol. Individual supervision will also be provided to all coaches during their first month as online coach. Hereafter, the support sessions between coaches and participants will be regularly checked at random. A forum, in the form of a secured Facebook community, will be available for questions and discussion of scenarios in between the face-to-face supervision sessions, and coaches will furthermore be free to contact the supervisors at any time.

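### Coach is absent from the sample size and the stated model, so contrasts of supported with unsupported conditions will look too precise if coach is left out of the analysis

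*Protocol article*

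**What the plan says.** The Study conditions section gives weekly coach support to condition two and three-times-weekly support to condition three. Condition one is automated and condition four is a waiting list.

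Under Support from a coach: "Support will be provided by master level students in clinical psychology or individuals with a degree in the field of psychology". They share training and supervision, and "All coaches will follow an intervention protocol that includes all guidelines for the provision of support". That section speaks of a participant e-mailing his or her own coach. It does not give the number of coaches, the caseload, how participants are assigned to coaches, or whether one coach may serve both supported conditions.

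The Sample size section defines the primary hypothesis as "the average post-intervention level of eating pathology in the waiting list control condition is higher than the average level" in the three active conditions. From a one-way ANOVA it concludes that "we need sample sizes of 79 participants in each of the four groups whose means are to be compared using a planned comparison". It then adjusts for a baseline covariate and for dropout, but not for clustering.

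The Statistical analyses section states "Linear mixed model analyses will be used to investigate the effectiveness and maintenance effects of Featback", with dummy-coded time contrasts. It names no random effect of any kind, and coach is not mentioned.

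**The concern.** The design is partially nested. Outcomes in two of the four conditions may share a coach, while participants in the other two stand alone. Participants of the same coach may respond more alike than participants of different coaches. If so, the mean of a supported condition carries coach-to-coach variation that does not shrink with the number of participants per coach.

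The Background and Discussion present the effect of support, and of its intensity, as the trial's particular contribution. Comparisons of supported with unsupported conditions carry this extra variation. A model without it gives intervals that are too narrow and too many false claims of a support effect.

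**Working it through.** **Inputs from the protocol article.** Sample size: Cohen's d = 0.32, alpha 0.05, power 0.80, baseline correlation 0.5, dropout 30%, giving 79, then 60, then 86 per group and 344 in total. Procedure and randomization: four equal groups. Statistical analyses: two-tailed 0.05. The supported conditions together hold 2 × 86 = 172 recruited participants, or 2 × 60 = 120 analysed.

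**Assumed, because the article gives neither.** Coach ICC of 0.01 to 0.05, and m = 6 to 20 participants per coach. With 120 analysed, that means 120/20 = 6 to 120/6 = 20 coaches.

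**Step 1: the plan's own figure.** For the waiting list against the mean of three equal groups, n per group = (4/3) × ((z_α + z_0.80)/0.32)².
- One-sided 0.05: 80.5, so 81. This is close to the stated 79.
- Two-sided 0.05: 102.2, so 103. This does not match.
- Later steps: 0.75 × 79 = 59.25, taken as 60; 60 × 10/7 = 85.7, so 86; 4 × 86 = 344.

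The figure is therefore a calculation for independent observations, with no design effect. The one-sided basis against two-tailed testing is a separate matter.

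**Step 2: design effect in the supported conditions.** DE = 1 + (m − 1) × ICC.
- Low end: 1 + 5 × 0.01 = 1.05.
- High end: 1 + 19 × 0.05 = 1.95.

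**Step 3: true variance divided by the variance assumed under independence.** Equal arms; DE applies to conditions two and three only. The true two-sided level is 2 × (1 − Φ(1.96/√ratio)).

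| Contrast | Variance ratio | Ratio, low to high | √ratio (standard error) | True level at nominal 5% |
|---|---|---|---|---|
| Both supported arms pooled vs basic | (1 + DE/2)/1.5 | 1.017 to 1.317 | 1.008 to 1.147 | 5.2% to 8.8% |
| One supported arm vs waiting list (or basic) | (1 + DE)/2 | 1.025 to 1.475 | 1.012 to 1.214 | 5.3% to 10.7% |
| Primary: waiting list vs three active | [1 + (1 + 2DE)/9]/(4/3) | 1.008 to 1.158 | 1.004 to 1.076 | 5.1% to 6.9% |
| Frequent vs infrequent, different coaches per arm | DE | 1.05 to 1.95 | 1.025 to 1.396 | 5.6% to 16% |
| Frequent vs infrequent, same coaches in both arms, balanced | 1 − ICC | 0.99 to 0.95 | 0.995 to 0.975 | 4.9% to 4.4% |

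In the one-arm row, m counts a coach's participants in that arm. If a coach's 6 to 20 participants are split evenly over both arms, m is 3 to 10 and DE is 1.02 to 1.45. The true level is then 5.1% to 7.7%.

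**Step 4: simulation.** 20,000 simulated trials, ICC 0.05, 10 participants per coach, 60 per arm, coach ignored.
- Pooled support vs basic: 6.8% with shared coaches, 6.9% with separate coaches.
- Frequent vs infrequent: 10.3% with separate coaches, 4.3% with shared coaches.

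The first result hardly depends on how coaches are assigned. The second changes direction with it.

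**Step 5: effect on the sample size.** Multiplying the plan's 60 by the primary-contrast ratio gives 60 × 1.0083 = 60.5 to 60 × 1.1583 = 69.5. Dividing by 0.7 gives 87 to 100 recruited per group, against 86.

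**The case against.** The strongest objection is that independence in the analysis is inferred. The article names a linear mixed model without any random effects, not even one for participant, and a condensed article commonly leaves that detail to the full plan. Coach is neither included nor ruled out. This stands: only the sample size shows independence directly, so the point about the analysis is conditional on coach being omitted.

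Second, caseload and coach numbers are not stated. This also stands, but one coach per participant is hard to credit with 172 supported participants. The Background itself treats finding enough coaches as a constraint.

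Third, a coach effect may be small. Support is optional, chat and Skype sessions last 20 minutes, coaches follow one protocol under supervision, and outcomes are self-reported. These features can lower the ICC but do not make it zero. The protocol also tests early working alliance as a predictor or moderator of response.

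Fourth, a reader might infer that every contrast on support is too precise. The article does not support that. If coaches serve both supported arms, the coach main effect largely cancels from frequent versus infrequent, and ignoring it makes that standard error slightly too large. Inflation would need coaches who differ by arm, or coach effects that do.

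**Conclusion.** The point holds in conditional form. If the coach ICC exceeds zero and coach is left out of the model, uncertainty for supported versus unsupported conditions is understated, modestly to moderately over the assumed range. The primary contrast is the least affected of these, because the waiting list and one active arm have no coach. For frequent versus infrequent support, even the direction of the error depends on a coach assignment that the article does not describe.

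The sizes rest wholly on the assumed ICC and caseload, and on equal arms and equal caseloads. The documents do not show that the planned analysis will in fact ignore coach. They show that the sample size does, and that the stated model gives no instruction to include it. This is a worthwhile and cheap improvement to the analysis, not a flaw that undermines the trial.

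**What to change.** The Trial status section reports enrolment complete, so the remedy lies in the analysis.

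- Record the coach identifier for each participant in conditions two and three, and state whether coaches serve one or both of these arms.
- Fit a partially nested mixed model: a random coach effect in conditions two and three only, with coaches crossed with arm or nested in it according to the actual assignment. Each participant in conditions one and four stands as his or her own cluster.
- Use small-sample degrees of freedom, since coaches may be few.
- If the coach variance is estimated as zero, report that, and add a sensitivity analysis over a plausible ICC range. Dropping the term without comment would return to the analysis criticised here, because with few coaches a real variance is often estimated as zero.

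The cost is one variance term and a coach identifier, which session records should be able to supply, although the article does not say that it is stored. The downside is slightly wider intervals for the supported conditions, and an imprecise variance estimate if coaches are few.
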